#### Phase 2 Consenting Procedures

All participants will provide signed consent to participate in this phase of the study. Eligible dyads will be sent an informed consent form electronically or as a hardcopy depending on their preference. Electronic forms will be distributed by email via an electronic-consenting platform and hardcopies will be sent by U.S. Mail. Similar steps used in phase 1 will be followed in phase 2 to obtain consent with the exception that both members of the dyad will provide signed consent, as opposed to verbal consent.

#### Phase 2 User Testing Procedures

Dyads will receive a toolkit and toolkit user guide by mail after collection of baseline data. Dyads will participate in an introduction session with a trained research team member via Zoom or phone to review how to use the toolkit. Dyads will use the toolkit in the home for 2 weeks. A 2-week duration was selected based on prior home-based studies with this population that have used HCD [48,49]. Dyads will be encouraged to use at least one tool from the toolkit at least once a day to manage day-to-day stress and to mitigate the risk of negative outcomes related to excess stress.

#### Phase 2 Measures

##### Aim 2

Usability will be measured by examining the frequency of use of the toolkit by participants. At the end of weeks 1 and 2 of user testing, dyads will complete a brief questionnaire to indicate tools that were used and by whom (ie, PLWD or care partner), number of days the toolkit was used over the past week, and each participant’s general response to the toolkit. The toolkit will be considered to have a high degree of usability if participants use it on average 9 or more days/14-day intervention period [28,50]. *Feasibility* will be measured throughout the study by examining several measures such as study enrollment and withdrawal rates, and adverse effects and injuries [51]. The prototype will be considered feasible if enrollment rate is 50% or more, withdrawal rate is 25% or less, and no adverse events or injuries were reported [52-54]. *Acceptability* will be measured at the end of week 2 of user testing. Dyads will complete item scales pertaining to what they found most beneficial and satisfying regarding the toolkit, and challenges experienced when using the toolkit. An acceptability survey will be developed for this study that will be modified from prior tools used to measure acceptability of nonpharmacologic dyadic-focused interventions for patients with chronic conditions and their care partners [55,56].

*Usability*, *feasibility*, and *acceptability* will be further explored through qualitative focus groups (3 groups in total; n=3-4 dyads/group) convened after participants have completed posttest questionnaires. Similar procedures used for focus groups in phase 1 will be used in phase 2 to explore the usability, feasibility, acceptability of the toolkit, and participants’ recommendations regarding modifications and refinements needed to improve the toolkit. Throughout the study, we will also keep a tracking sheet of the specific tools and cost of each toolkit delivered to participants in phase 2. We will ask questions pertaining to cost during the focus groups to begin to explore participants’ perceptions of cost and willingness to pay for such a toolkit out-of-pocket as a component of acceptability [57].

##### Aim 3

*Stress-related participant-reported outcomes* (eg, neuropsychiatric symptoms of dementia, caregiver stress, dyadic relationship strain) measured using psychometrically sound measurement tools [32,42,45] and *salivary cortisol biospecimens* of participants with dementia and care partners [58] will be collected at baseline and after user testing (Figure 1 and Tables 3 and 4). Outcome measure collection will be feasible if the measure can be collected in 80% or more of participants at baseline and after data collection timepoints.

**Table 3 table3:** Phase 2 outcome measures for aim 2.

Outcome	Measure	Measurement	Data collection tool
Usability	Frequency of toolkit use	How many days in the past week was the toolkit used by the participant with dementia/care partner? (range 0-7 days)	Questionnaire
Feasibility	Enrollment rate	Percentage of participants enrolled	Study tracking sheet
	Withdrawal rate	Percentage of participants that withdraw	
	Adverse events/injuries	Number of adverse events and injuries	
Acceptability	Satisfaction	Toolkit satisfaction scale (1=not satisfied at all to 5=very satisfied)	Questionnaire
	Perceived benefit	Toolkit benefit scale (1=not at all beneficial to 5=very beneficial)	

**Table 4 table4:** Phase 2 outcome measures for aim 3.

Outcome	Measurement	Psychometric properties	Data collection tool
Neuropsychiatric symptoms of dementia	Neuropsychiatric Inventory-Questionnaire [34]	Cronbach α (range)=.71-.88 Percentage agreement between raters: 93.6%-100% Test-retest reliability range (r)=0.79-0.86 [34,59,60]	Questionnaire
Caregiver stress	Perceived Stress Scale [43]	Cronbach α (range)=.75-.82 External validity established through CFA^a^ [42,44]	Questionnaire
Dyadic relationship strain	Dyadic Relationship Scale [45]	Cronbach α (range)=.84-.89 External validity established through CFA [45]	Questionnaire
Physiologic stress	Salivary cortisol biospecimens	N/A^b^	Oral swab

^a^CFA: confirmatory factor analysis.

^b^N/A: not applicable.

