### Phase 2: Validate (Aims 2 and 3)

Phase 2 will address the *validate* step of the HCD process (Table 1). A total of 10 dyads (who were not involved in phase 1) will use the prototype toolkit for 2 weeks and measures of usability, feasibility, acceptability, and stress-related outcomes will be collected (Figure 1).

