#### Phase 2 Participants and Recruitment

Similar eligibility criteria will be used in phase 2 as were used in phase 1 with few additional criteria to address contraindications to the collection of salivary cortisol biospecimens. In addition to the phase 1 criteria, participants will be excluded if they (1) currently receive cytokine-based therapy; (2) currently receive radiation therapy to the salivary glands or thyroid; (3) are diagnosed with Cushing or Addison disease. Dyads will also be excluded in phase 2 if they participated in phase 1. The same recruitment strategy used in phase 1 will be used in phase 2 as well. Ten dyads was selected as the projected sample based on prior studies that have used HCD with this population [26,27], but up to 20 may be enrolled if data saturation is not reached.

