#### Phase 2 Data Collection

##### Aim 2

Feasibility data will be collected by the research team throughout the study using a tracking sheet stored on a secure institutional server. Usability and acceptability data will be collected using questionnaires completed electronically, by hardcopy, or verbally by phone in accordance with participant preference. Similar data collection procedures described in phase 1 will be used to collect questionnaire data in phase 2. Sociodemographic and diagnosis characteristics of the dyad will also be collected using a questionnaire. Similar qualitative data collection procedures used in phase 1 will be used to collect focus group data in phase 2.

##### Aim 3

*Stress-related participant-reported outcome measures* will be collected using questionnaires completed electronically, by hardcopy, or verbally by phone, depending on participant preference. *Salivary cortisol biospecimens* will be collected by participants using oral swab kits. Participants with dementia and care partners will each provide 10 samples in total. Five samples (per participant) will be collected over the course of 1 day at baseline and the remaining 5 will be collected over the course of 1 day after data collection. Participant dyads will receive sample kits by postal mail at least one week prior to the 2 data collection timepoints (baseline and after). Each dyad will participate in a telephone or Zoom session with a research team member to review how to collect saliva samples prior to the scheduled data collection timepoint. During this session, participants will be asked to not complete the sample collection if any of the following are present on the day of data collection: (1) a fever >101°F, (2) upper respiratory infection with nasal drainage, and (3) inflammation of the throat. As appropriate, an alternative day will be identified if any of these symptoms are present, or the data collection will be canceled and documented as incomplete in the study database.

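### The feasibility rule fails the prototype on any single reported adverse event, whether or not the toolkit caused it, and becomes harder to pass if enrolment is extended

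*Protocol article*

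**What the plan says.** All of this is in the protocol article.

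- **The measure, as introduced (Phase 2 Measures, Aim 2).** Feasibility "will be measured throughout the study by examining several measures such as study enrollment and withdrawal rates, and adverse effects and injuries".
- **The rule, two sentences in one.** Its first two conditions are given as "The prototype will be considered feasible if enrollment rate is 50% or more, withdrawal rate is 25% or less". A third condition, which must hold as well, reads "and no adverse events or injuries were reported". The three conditions are joined by *and*. The third has no qualifier for relatedness, severity or timing.
- **Table 3.** The corresponding entry is "Number of adverse events and injuries", also unqualified.
- **Sample size.** Under Phase 2: Validate, "A total of 10 dyads (who were not involved in phase 1) will use the prototype toolkit for 2 weeks". Under Phase 2 Participants and Recruitment, "up to 20 may be enrolled if data saturation is not reached".
- **Timing (Phase 2 User Testing Procedures).** The toolkit is mailed only once baseline data are in.
- **Pilot (Preliminary Studies).** A weighted-blanket study in 21 dyads, with use reported out of 30 days, had no injuries or adverse events.
- **Use of the result.** Future Directions makes a larger randomised trial the next step if feasibility and acceptability are shown.

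**The concern.** An adverse effect is something the toolkit did. An adverse event is anything untoward that happened while the person was under observation. The measure is introduced with the first term and judged with the second, and the broader term decides the result. No other part of the article says which events count.

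Two consequences follow from the wording.

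- **Timing.** Feasibility is tracked over the whole study, so an event between enrolment and delivery of the toolkit would count against a toolkit the dyad did not yet have.
- **Sample size.** A zero-count rule gets stricter as people are added. The enrolment and withdrawal conditions are proportions and do not behave this way. The reason given for adding dyads is data saturation, which has nothing to do with safety.

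What is at stake is the feasibility label that informs the decision on an efficacy trial. If an unrelated event occurs, the team must either declare a harmless toolkit infeasible or decide after seeing the data that the event does not count. The second choice would undercut the predefined measures that the Discussion lists as a strength.

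**Working it through.** The article states no error rate or pass probability for this rule, so there is no figure to reproduce. The check asks how often a harmless toolkit would fail.

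**Inputs**
- 10 dyads = 20 people (projected); 20 dyads = 40 people (maximum).
- Events allowed: 0.
- p = probability that a person has at least one reported event unrelated to the toolkit during the period counted. **The document does not give p.** Values of 1%, 2% and 5% are assumed.

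**Step 1. Chance of failing from unrelated events alone.** P(fail) = 1 − (1 − p)^n, where n is the number of independent units. If people are independent, n is the number of people. If both members of a dyad always have events together, n is the number of dyads. Dyad members share a household, so the truth lies between these two cases.

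| Assumed p | 10 dyads, events coincide (n=10) | 10 dyads, independent people (n=20) | 20 dyads, independent people (n=40) |
|---|---|---|---|
| 1% | 1 − 0.99^10 = 10% | 1 − 0.99^20 = 18% | 1 − 0.99^40 = 33% |
| 2% | 1 − 0.98^10 = 18% | 1 − 0.98^20 = 33% | 1 − 0.98^40 = 55% |
| 5% | 1 − 0.95^10 = 40% | 1 − 0.95^20 = 64% | 1 − 0.95^40 = 87% |

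For 20 dyads with coinciding events, n = 20, so the middle column applies.

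**Step 2. Where failure becomes more likely than not.** Solve 1 − (1 − p)^n = 0.5, which gives p = 1 − 0.5^(1/n). With independent people this is 3.4% for n = 20 and 1.7% for n = 40.

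**Step 3. What the pilot says about p.** Assume its zero events cover 42 people for 30 days at a constant rate.
- Exposure is 42 × 30 / 14 = 90 person-fortnights. The chance of zero events is 0.98^90 = 16% at p = 2% and 0.95^90 = 1% at p = 5%. If only the 21 people with dementia were monitored, exposure is 45 person-fortnights and the chances are 0.98^45 = 40% and 0.95^45 = 10%.
- For 42 people, the one-sided 95% upper bound on the daily rate is −ln(0.05) / (42 × 30) = 0.00238. Over 14 days this is 1 − exp(−14 × 0.00238) = 3.3% per person.
- At that bound, P(fail) with 20 independent people is 1 − exp(−20 × 14 × 0.00238) = 49%.

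The pilot therefore favours low rates and fits poorly with 5%, but it does not exclude about 3% per person per two weeks. It also tested a single tool.

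**Step 4. Contrast with the neighbouring condition.** The 25% withdrawal limit tolerates 2 of 10 dyads (20%; 3 of 10 would be 30%). The adverse-event condition tolerates none.

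**Step 5. Effect of counting related events only (illustration).** If an assumed 10% of events were related, P(fail) with 20 independent people would be 1 − 0.998^20 = 4% instead of 33% at p = 2%, and 1 − 0.995^20 = 10% instead of 64% at p = 5%.

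**The case against.** The strongest defence has four parts.

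- **Narrower reading.** The introducing sentence speaks of adverse effects, and the rule is about the prototype. A full protocol, not shown, may define which events count. This is possible, but the rule and Table 3 both use the broader term, so the article's text still has to be reconciled.
- **Low event rates.** The pilot had no events. This stands in part: it makes the upper end of the assumed range less plausible and leaves about 3% open.
- **Conservative choice.** Zero tolerance can be defended in a vulnerable group, and an attribution step adds discretion. That is a fair cost. It does not justify counting events that the toolkit cannot have caused.
- **Small descriptive study.** Feasibility is also explored in focus groups, and no automatic stop is written. This lowers the consequence of a failed label but does not change what the label means.

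Stronger readings are tempting, and the document does not support them.

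- A reader might infer from the saliva-sampling instructions, which list "upper respiratory infection with nasal drainage" among other conditions, that the plan expects such illness and would record it as an adverse event. The list is conditional. It gives reasons to postpone or cancel a collection and does not call these conditions adverse events.
- A reader might infer that a harmless toolkit would often fail. That depends on an event rate the document does not give.
- A reader might infer that passing would require under-reporting. Nothing in the document supports this, and at low rates the rule is passed most of the time.

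**Conclusion.** The concern holds as a defect in a stated decision rule. As written, one reported adverse event of any cause, at any time in the study, makes the prototype infeasible, and the text uses two different terms for what is counted. With 10 dyads, the chance of such a failure for a harmless toolkit runs from about 10% to 18% at an assumed p of 1%, and from about 18% to 33% at 2%. The lower figure assumes complete coincidence within dyads and the upper assumes independence. At 5% the range is 40% to 64%, but the pilot makes that rate less likely. Doubling enrolment raises the independent-people figures to 33%, 55% and 87%.

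These sizes rest on assumed rates and on the assumption that all unrelated events are reported and counted. The reading of the rule and its tightening with enrolment do not depend on the value chosen for p, provided it is above zero.

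**What to change.** - Use one term in the Aim 2 text and in Table 3, and state which events it covers.
- Limit the feasibility criterion to events or injuries judged related to the toolkit and occurring after its delivery.
- Report all adverse events and injuries descriptively, by relatedness and by role (person with dementia, care partner), outside the pass rule.
- If a proportion of dyads replaces the zero count, so that the rule does not tighten with enrolment, the sponsor should fix the threshold in advance. The document offers no basis for a particular value, and none is proposed here.

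The cost is a sentence or two in the protocol, a matching edit to Table 3, and columns for relatedness and date on the existing tracking sheet. The downside is that relatedness becomes an investigator judgement in a study without a control group. Publishing the full table of events lets readers check that judgement.

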Prior studies have primarily relied on participant-reported outcomes to measure outcomes of stress, and most have focused solely on care partner–specific outcomes. Participant-reported outcomes are useful indicators of psychosocial components of stress, but they can be difficult to collect among PLWD and are subject to inherent risk of bias when completed by proxy report [23,24]. Including biomarkers of stress as outcomes can mitigate limitations of self-report as physiologic stress reactivity is associated with self-reported stress levels among older adults [25]. Physiologic measures of stress may provide a nuanced understanding of intervention efficacy when supplemented with more traditional participant-reported stress outcomes [7]. A multipronged approach to measuring individual and dyadic stress that captures the biopsychosocial nature of the stress process is critical to examining the impact of interventions on dementia caring dyads [7]; however, the feasibility of collecting physiologic measures of stress in this population needs to be determined prior to use in efficacy trials.

The overarching goal of this study is to design a prototype of a dyadic, tangible stress management toolkit with *and* for PLWD and their families [19]. Using a human-centered design (HCD) approach that prioritizes stakeholder engagement at the outset, PLWD and care partners will collaborate with the research team to create the toolkit using 4 key design steps (discover, define, design, and validate) to optimize the intervention for future use (Table 1) [20,26,27].

The *specific aims* of this study are to:

Aim 1: Develop a prototype of a dyadic stress management toolkit with and for PLWD and their care partners.Aim 2: User test the dyadic stress management toolkit intervention with 10 PLWD and their care partners.Aim 3: Explore the feasibility of collecting stress-related outcome measures in dyads participating in user testing, including participant-reported outcomes (ie, neuropsychiatric symptoms of dementia, caregiver stress, dyadic relationship strain) and salivary cortisol biospecimens as a physiologic measure of stress.

**Table 1 table1:** Human-centered design steps addressed through study phases 1 and 2.

Phase and aim	Step and definition

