#### Phase 2 Data Analysis

##### Aim 2

Descriptive statistics (means, SDs, frequencies, percentages) will be calculated for measures of usability, feasibility, and acceptability. Similar rapid qualitative analysis methods that were used in phase 1 will be used to analyze phase 2 focus group data.

##### Aim 3

Percentage of participants with data collected will be calculated for each outcome measure at each data collection timepoint. To further describe the study sample, the Neuropsychiatric Inventory, Perceived Stress Scale, and Dyadic Relationship Scale measures will be scored for each participant according to measurement scoring guidelines at each timepoint and group means (SDs) will be calculated. We will not assay the salivary cortisol specimens in this study, but will do so as a secondary analysis in a future study.

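### For measures taken from both dyad members, the 80% collection rule is not split by role, so it can be met with data from only 60% of people with dementia

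*Protocol article*

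**What the plan says.** The rule is in the protocol article, Phase 2 Measures, Aim 3, where collection of an outcome measure is called "feasible if the measure can be collected in 80% or more of participants at baseline and after data collection timepoints". Phase 2 Data Analysis, Aim 3, gives the matching summary: "Percentage of participants with data collected will be calculated for each outcome measure at each data collection timepoint". Neither sentence mentions role.

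Phase 2 plans for 10 dyads ("A total of 10 dyads (who were not involved in phase 1) will use the prototype toolkit for 2 weeks"), and "up to 20 may be enrolled if data saturation is not reached".

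Who supplies each Aim 3 measure:

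- **Salivary cortisol:** both members. Phase 2 Data Collection, Aim 3, has each of them give 10 samples, and the swab counts there are per participant.
- **Dyadic Relationship Scale:** Table 2 (phase 1) lists a 10-item version for PLWD and an 11-item version for care partners. Table 4 (phase 2) does not say which versions are used.
- **Perceived Stress Scale:** listed in Table 4 under caregiver stress only.
- **Neuropsychiatric Inventory-Questionnaire:** describes the PLWD's symptoms. Its phase 2 respondent is not stated.

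On withdrawal, Phase 2 Measures, Aim 2, requires that "withdrawal rate is 25% or less", and Table 3 defines the measure as "Percentage of participants that withdraw".

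**The concern.** Aim 3 asks whether these measures can be collected in dementia caring dyads. The Background section says that the feasibility of physiologic measures in this population has to be established before they are used in efficacy trials. Where both members contribute, one percentage over all individuals can be carried by one role. If the shortfall lies among PLWD, the rule can return a favourable answer while a large minority of them gave no data.

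This matters most for cortisol. The samples will not be assayed in this study, so the collection percentage is the main quantitative result on cortisol available to the planners of the next trial.

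**Working it through.** The article gives no power or sample-size calculation for these criteria, so there is no figure of its own to reproduce. The check turns the threshold into counts and then into pass probabilities.

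**Inputs from the article.** 10 dyads (20 individuals), or at most 20 dyads (40 individuals); threshold 80% of participants.

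**Inputs assumed.** The article gives no collection rate by role. I take PLWD at 60% and care partners at 90%, 95% and 100%, with the two members of a dyad independent, and consider one timepoint.

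**Step 1: lowest PLWD rate that still passes.** This step needs no assumption about rates.

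- 10 dyads: 0.80 × 20 = 16 needed. With all 10 care partners, 16 − 10 = 6 PLWD suffice, and 6/10 = 60%.
- 20 dyads: 0.80 × 40 = 32 needed. With all 20 care partners, 32 − 20 = 12 PLWD suffice, and 12/20 = 60%.

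In both cases the share of complete dyads is also 60%.

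**Step 2: chance of passing, 10 dyads.** Let X ~ Bin(10, care partner rate) and Y ~ Bin(10, 0.60). The combined rule passes if X + Y ≥ 16. PLWD judged alone pass if Y ≥ 8.

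P(Y ≥ 8) = 0.1209 + 0.0403 + 0.0060 = 0.167.

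| Care partner rate | Combined rule passes | PLWD alone pass | Combined passes while PLWD are below 80% |
|---|---|---|---|
| 90% | 0.404 | 0.167 | 0.246 |
| 95% | 0.513 | 0.167 | 0.347 |
| 100% | 0.633 | 0.167 | 0.466 |

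**Step 3: 20 dyads.** With PLWD at 60% and care partners at 95%, the combined rule passes with probability 0.426, against 0.051 for PLWD alone (Y ≥ 16 of 20). The larger sample does not remove the gap.

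**Step 4: cost of requiring both roles to pass.** If both true rates are 80%, one role of 10 passes with probability P(Bin(10, 0.80) ≥ 8) = 0.678. Both pass with probability 0.678² = 0.459. The combined rule passes with probability P(Bin(20, 0.80) ≥ 16) = 0.630.

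**Step 5: where the problem can arise.** It needs two respondents per dyad. That is clear for cortisol and conditional for the Dyadic Relationship Scale. It cannot arise for caregiver stress, which has one respondent per dyad. It apparently cannot arise for the Neuropsychiatric Inventory-Questionnaire, which rates only the PLWD.

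**Step 6: withdrawal.** Counted over individuals, 0.25 × 20 = 5 withdrawals are allowed. If members could leave singly, all five could be PLWD, 5/10 = 50%. If dyads leave together, at most 2/10 dyads may withdraw (3/10 = 30% exceeds the limit), and nothing is hidden.

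**The case against.** **Pooling is not expressly stated.** This is true. Phase 2 separates the roles elsewhere: the usability questionnaire asks who used each tool, and the phase 1 procedures that carry over have separate questionnaires for each member. Reporting by role is compatible with the text, and a condensed article may leave detail to a fuller document. But the article does fix the pass/fail rule and its breakdown, and for saliva it uses the word participants for both members. Counting all individuals is the plain reading.

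**The plan does not predict poor saliva collection in PLWD.** A reader might infer that it does, and that care partners are expected to comply. Neither is supported. The Background remark that "they can be difficult to collect among PLWD" concerns participant-reported outcomes, and biomarkers are offered there as a way round self-report limits. Nothing is said about care partner compliance. The 60% rate is therefore an illustration.

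**The probabilities are fragile.** They treat members as independent, although care partners may help collect the PLWD's samples and training is given per dyad. They also cover one timepoint, while the rule names two. If timepoints were independent, care partners at 95% would give 0.513² = 0.263 combined, against 0.167² = 0.028 for PLWD alone. The levels change, but the combined rule is still the easier one to pass. The 60% floor depends on none of this.

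**Withdrawal.** A reader might infer that half the dyads could break up within the 25% limit. The article neither describes nor excludes one member leaving while the other stays. Table 3 also defines enrollment over participants, although recruitment and consent are dyadic, so that word does not establish individual counting there.

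**Consequences.** The results inform measurement selection and do not bind a future trial. That is fair, and it limits what is at stake.

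**Conclusion.** The point holds for salivary cortisol, and for the Dyadic Relationship Scale if phase 2 uses both versions. For these, the 80% rule as worded can be met with data from 60% of PLWD, at 10 or at 20 dyads. That floor is arithmetic and rests only on reading participants as all individuals.

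The size of the risk rests on assumed rates. With PLWD at 60% and care partners at 90% to 100%, independent members, one timepoint and 10 dyads, the rule passes 40% to 63% of the time, against 17% for PLWD judged alone.

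The point does not extend to all four Aim 3 measures. For withdrawal it supports only a request to state the unit of counting.

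**What to change.** For every measure that both members provide:

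- apply and report the 80% rule separately for PLWD and for care partners at each timepoint;
- call the measure feasible in dyads only if both roles meet it;
- report the percentage of dyads with both members' data.

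State in Table 4 who completes each measure, so that it is clear which ones this covers. With 10 dyads, each role then needs at least 8/10; with 20 dyads, at least 16/20.

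As a secondary clarification, state that the 25% withdrawal limit is counted per dyad, and report which member withdrew.

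The cost is a change of wording and a few extra rows in the results, with no new data, participants or visits. The criterion becomes stricter: with both true rates at 80%, it passes about 46% of the time at one timepoint, against 63% for the combined count. The choice should be made before the collection percentages are seen, because the denominator could decide the result.
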